#### Eligibility

The following criteria are used to check eligibility for participation in the trial:

Completion of a curative-intent treatment for cancer at least 3 months ago (checked by participant’s medical doctor). For this study, surgery, chemotherapy, radiotherapy, immunotherapy, and/or stem cell transplantation are considered treatment. However, hormonal therapy, the use of anti-inflammatories, and monitoring visits are not considered treatment for this study.Patient has been suffering from severe fatigue for at least 3 months.Patient scores 35 or higher on the fatigue severity subscale of the Checklist for Individual Strength (CIS).Aged 19 years old or older.At least 18 years old at disease onset.Capable of reading and writing in the Dutch language and of using the Internet (implicit eligibility criterion accounted for during registration, but not checked explicitly).

If patients meet 1 or more of the following criteria, they are excluded from participation:

Indication of current disease or tumor activity (checked by the participant’s medical doctor).Current or former severe psychiatric morbidity, for example, major depression, psychosis, or schizophrenia (checked by the participant’s medical doctor).Being dependent on a wheelchair for daily activity (self-report).Recurrence of cancer during the course of the study (self-report).Current substance abuse, except for smoking.Previously attended the eMBCT of the Helen Dowling Institute.

In addition to the mentioned exclusion criteria, please note that:

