### Outcome Measures

#### Fatigue

Fatigue severity will be assessed with the CIS, which consists of 20 items that score on a 7-point Likert scale [53,54]. The CIS has 4 subscales (fatigue severity, motivation, concentration, and physical fatigue) of which the fatigue severity subscale will be used as the primary outcome (8 items, range: 8-56 points). The CIS has shown good discriminative validity in a working population [55], is sensitive to changes in the chronic fatigue syndrome population [56], and has previously been used with cancer survivors [7,57]. The CIS strongly resembles the Multidimensional Fatigue Inventory, which is often used in international studies [54]. Fatigue severity will be assessed at T0a, T0b, M3, M6, M9, T1, T2, and T3. However, the other 3 subscales will only be assessed at T0b, T1, T2, and T3.

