##### Descriptives

Quantitative analyses will be conducted on an intention-to-treat basis. A flow diagram following the CONSORT guidelines will be included. Descriptive statistics will be calculated and presented. Independent samples’ t-tests and χ^2^ tests will be performed to check for baseline differences between the respective experimental conditions and the control condition with respect to demographic variables (eg, family status, age, gender, and level of education), time since end of treatment, and baseline levels of the outcome variables. If we find statistically significant differences in the mean of fatigue severity across baseline descriptives, dummy variables will be added to the model as covariates to control for these differences.

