Hypotheses on mediators.We expect that, for AAF, increasing mean cumulative daily physical activity and reductions of daily physical activity decline are specific mediators.We expect that, for eMBCT, developing mindfulness skills is a specific mediator.We expect that sleep quality, working alliance, sense of control over fatigue, credibility, and expectancy are generic mediators for both e-therapies.The mediating role of the following factors will be explored: number of sessions completed, changes in causal attributions [99], decreased catastrophizing thoughts about fatigue [8], decreased fear of cancer recurrence [100,101], changes in perceived activity [102], increased self-efficacy on physical activity [103].

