**Figure 5 figure5:**
[figure not shown]
Simplified representation of a correlated growth model in which Iy and Sy represent the intercept and slope factors of the latent growth model of the outcome parameter, and Iz and Sz represent the latent growth factors of the mediator. H1-4 represent the 4 subhypotheses of Step 6. All indicators have been left out for clarity.

###### Step 7

The next step in studying potential working mechanisms is a single-step, multiple-mediation analysis using structural equation modeling [104-106]. By estimating such a model, we expect to obtain a comprehensive model for all the working mechanisms of the intervention. It should be noted that this model assumes that an intervention works in the same way for all participants in a particular group [107]. Again, data from both semesters will be used.

A separate model will be tested for each intervention. Each model will have the following paths (Figure 6), where X=independent variable (1/0 for specific intervention vs control group), Y=outcome variable (difference score T2-T0b of the primary outcome measure), and Z=mediator:

a: X regressed on Z.b: Z regressed on Y;c’: direct effect of X on Y.

For each experimental intervention, the starting model will consist of all the significant primary mediators of Step 6 that have also been assessed in the control group. In other words, the factors that have shown to be mediators in the correlated growth model will be the starting point for this model. The models will then be complemented with the secondary mediating factors described in Textbox 2. Mediating factors for which the indirect effect (a × b) is insignificant will be removed stepwise, after which a final model will be created.

Model fit, standardized path coefficients—including indirect effects—and the total effect of at least the first and final models will be reported with 95% confidence intervals.

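### Step 7 analyses a T2-T0b change score with no baseline fatigue term, so the mediator path, the indirect effect and the direct effect rest on an unstated assumption about baseline

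*Protocol article*

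**What the plan says.** Under Mediators, Step 7, the protocol article fits one structural equation model per intervention, with "X=independent variable (1/0 for specific intervention vs control group") and "Y=outcome variable (difference score T2-T0b of the primary outcome measure"). The listed paths are a, b and "c’: direct effect of X on Y". No path from T0b fatigue and no other covariate is named. Figure 6 is not shown; its caption mentions only X, Y, two mediators, and the direct and indirect effects. Mediators whose a x b is not significant are removed stepwise.

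Three related statements matter:

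- **Form of Z.** Step 7 does not say whether a mediator enters as a level, a change or a slope. Textbox 2 words some as changes, for example "changes in causal attributions [99], decreased catastrophizing thoughts about fatigue [8"].
- **Data.** "Again, data from both semesters will be used", so control participants who start an intervention after T2 contribute as well.
- **Covariates.** The only covariate rule is under Descriptives. If fatigue severity differs significantly across baseline descriptives, "dummy variables will be added to the model as covariates to control for these differences". This rule is conditional, does not name baseline fatigue as the covariate, and is not tied to Step 7.

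The data for an adjustment exist: "Fatigue severity will be assessed at T0a, T0b, M3, M6, M9, T1, T2, and T3". Table 2 also shows a T0b value for most mediators.

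**The concern.** A change score does not remove the influence of the starting value unless the slope of T2 on T0b is 1. With a slope below 1, as is usual for a fallible questionnaire repeated after months, participants with high T0b fatigue tend to fall more. Sense of control, sleep quality and mindfulness may well be related to T0b fatigue. If so, part of that fall is credited to the mediator through b. Random allocation does not prevent this, because participants are not randomised to levels of Z.

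Mediators are the trial's second objective, and a x b decides which factors stay in the final model. The handling of baseline could therefore change which working mechanisms are reported.

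**Working it through.** **The plan's own figure.** The only number tied to the mediator analysis is the approximately 254 participants under Power Analyses. A noncentral F calculation with 6 numerator degrees of freedom, f2 = .08, alpha = .05/6 and power .80 gives 252, so it reproduces closely. It says nothing about bias in b, and the documents give no bias figure.

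**Inputs**

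| Input | Value | Source |
|---|---|---|
| Expected N at T2 for one Step 7 model, first semester | 77 + 94 = 171 | Power Analyses |
| Slope of T2 on T0b fatigue, β0 | .3 to .7 | assumption |
| Within-arm slope of T0b fatigue on Z, γ | -.1 to -.5 | assumption |
| Path a | 0.4 SD | assumption |

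All variables have SD 1 within arm. In that scale γ equals the within-arm correlation and β0 the T0b-T2 correlation when true b is 0.

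**Step 1: Z is a level and baseline fatigue itself drives T2.** Write T2 = β0·T0b + b·Z + c'·X + error. Then T2 - T0b = (β0 - 1)·T0b + b·Z + c'·X + error. Leaving out T0b shifts b by (β0 - 1)·γ:

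| β0 | γ = -.1 | γ = -.3 | γ = -.5 |
|---|---|---|---|
| .3 | +0.07 | +0.21 | +0.35 |
| .5 | +0.05 | +0.15 | +0.25 |
| .7 | +0.03 | +0.09 | +0.15 |

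The shift is zero if γ = 0 or β0 = 1. Take β0 = .5 and γ = -.3:

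- True b = 0: estimated b = (.5 - 1)(-.3) = +0.15.
- True b = -0.30: estimated b = -0.30 + 0.15 = -0.15, and a x b = 0.4 × -0.15 = -0.06 instead of -0.12.
- c' shifts by -a times the shift in b, that is -0.4 × 0.15 = -0.06, so a true -0.10 becomes -0.16.
- The shifts in c' and in a x b cancel, so the randomised total effect is not biased in first-semester data.

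Simulation with 400,000 records gave the same values to within 0.01. A true b between 0 and -0.15 would change sign.

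**Step 2: rejection rate for b alone.** With N = 171, true b = 0 and β0 = .5 (4,000 replicates), P < .05 occurred as follows:

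| γ | Change score | With T0b covariate |
|---|---|---|
| 0 | 5.5% | 5.3% |
| -.1 | 10% | 5% |
| -.3 | 50% | 5% |

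**Step 3: Z is also a change score.** Let the mediator's stability be s and true b = 0. The covariance of the two changes is (-.5)·(-(1 - s))·(-.3) = -.15(1 - s). The variance of the mediator change is 2(1 - s). Hence b = -.15/2 = -0.075, whatever s is. Simulation gave -0.08 at s = .5 and .7. The shift has the opposite sign and half the size.

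**Step 4: the same correlations from a stable unmeasured trait.** Let T0b and T2 correlate .5, let Z correlate -.3 with both, and let true b = 0.

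- Change score on Z: -.3 - (-.3) = 0, so b = 0.00.
- T2 adjusted for T0b: [-.3 - (-.3)(.5)]/(1 - .3²) = -.15/.91 = -0.165.

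Simulated variants of this case put the adjusted b at about -0.11 to -0.17, with P < .05 for b in 19% to 67% of trials. In a setting with a stronger trait, change on change gave 0.00, while adjusting for both baseline fatigue and baseline Z gave -0.21.

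**Step 5: precision of the total effect.** With equal variances at T0b and T2, the variance ratio of unadjusted change to adjusted T2 is 2(1 - r)/(1 - r²) = 2/(1 + r). This is 1.54, 1.33 and 1.18 for r = .3, .5 and .7. At r = .5, with 77 and 94 participants, 1/77 + 1/94 = 0.0236. The standard error is √0.0236 = 0.154 for the change score and √(.75 × 0.0236) = 0.133 after adjustment.

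**The case against.** The strongest objection is that change score versus baseline adjustment is a recognised choice for a non-randomised exposure, and that it rests on a causal assumption the data cannot test. Step 4 of the working bears this out. A stable trait is plausible in a chronically fatigued sample, and adjustment would then create spurious mediators in the hypothesised direction. This stands. A reader might infer that the plan's choice is simply biased and should be replaced by baseline adjustment; the documents do not support that.

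Other points on that side:

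- **Entry criterion.** Eligibility requires "Patient scores 35 or higher on the fatigue severity subscale of the Checklist for Individual Strength (CIS"), and a reader might infer that this cut-off makes the distortion worse. The cut-off acts on T0a, whereas Y uses the separate T0b score. A mean shift common to both arms does not bias b. Selection also narrows the baseline spread, which weakens the link between mediator and baseline while possibly lowering β0, so the net direction is not determined. The argument cannot be used.
- **Error rates.** The percentages above are for b alone. Step 7 decides on a x b, and primary mediators must first pass Step 6. They should not be read as false-positive rates for declared mediators. For a protective mediator entered as a level, the shift runs against the hypothesis.
- **Form of Z and completeness.** Z may be a change, and the article may omit covariates that stand in a fuller document. That limits the certainty. But Y itself is stated, and the bias formulas show that either form of Z can be affected.
- **Baseline values.** Working alliance and number of sessions completed have no baseline value. Credibility and expectancy are first measured at T0c, after randomisation. Adjustment is therefore not available for every mediator.

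**Conclusion.** The point holds as a conditional one. Step 7 fixes a change-score outcome, names no baseline fatigue term and leaves the form of Z open, so b, a x b and c' depend on an assumption that the plan does not state. Distortion is likely if the mediator is related to T0b fatigue within arm and β0 is below 1. For mediators entered as levels that are higher when fatigue is lower, the main risk is a hidden or sign-reversed indirect effect, not a falsely confirmed one.

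The size cannot be taken from the documents. It is about 0.15 SD in b at β0 = .5 and γ = -.3, between 0.03 and 0.35 SD over the grid, and zero under the stable-trait explanation, where adjustment is instead biased by about -0.165. The gain in precision for the total effect does not depend on which explanation is true, only on the assumed correlation.

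This concerns a secondary, mechanistic analysis. A reader might infer that the effectiveness result is at risk as well. It is not: Step 1 uses a latent growth model and not this change score.

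**What to change.** Before the mediator analysis:

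1. State for each mediator whether Z enters as a level or a change.
2. Add T0b fatigue as a covariate on both Y and Z. Add the baseline level of each mediator that has a T0b value. Do not do so for working alliance, credibility and expectancy, or number of sessions.
3. For second-semester records, define Y and the covariates from the pre-treatment and post-treatment scores of that semester. For these participants T2 is the pre-treatment score, so T2-T0b does not describe their response. Table 2 shows no T2 value for physical activity, catastrophizing and some other mediators, so their second-semester baseline needs an explicit rule.
4. Report the change-score model alongside, and call a factor a mediator only if its indirect effect holds in both models.

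The adjustment needs no new data where a T0b value exists. The cost is a second set of models and a more conservative claim. If baseline fatigue does drive T2, the change-score model weakens true indirect effects (by half in the -0.30 example), and the two-model rule will miss some of them.

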**Methods:**

A 3-armed randomized controlled trial is proposed that compares both Internet interventions with an active control condition that solely consists of receiving psycho-educational emails. The intervention period is 9 weeks for all 3 conditions. Six months after baseline, participants in the control condition can choose to follow 1 of the 2 experimental Internet interventions. Outcomes are measured in terms of fatigue severity, mental health, and self-perceived work ability. All are Web-assessed at baseline, 2 weeks after the intervention period, and at 6 and 12 months after baseline. Fatigue severity, mindfulness, physical activity, expectations and credibility of the intervention, therapeutic working alliance, sleep quality, and sense of control over fatigue are assessed 3 times during the intervention period for identifying mediators of the interventions. Recruitment is performed nationally throughout the Netherlands through patient organizations and their websites, newspapers, and by informing various types of health professionals. All participants register at an open-access website. We aim at including 330 cancer survivors who have finished curative-intent cancer treatment at least 3 months previously, and have been suffering from severe fatigue ever since. All cancer types are included. A detailed analysis plan is described to address the research questions, which allows for individual variation, and fully exploits the longitudinal design.

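### Read naturally, Step 7 tests number of sessions completed as a mediator against a control arm that has no sessions, so its a × b would not be an indirect effect of randomisation

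*Protocol article*

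**What the plan says.** Textbox 2 (hypotheses on mediators) closes with a list of exploratory factors: "The mediating role of the following factors will be explored: number of sessions completed", followed by causal attributions, catastrophizing, fear of recurrence, perceived activity and self-efficacy.

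Step 7 fits a separate model for each intervention, with "X=independent variable (1/0 for specific intervention vs control group") and "Y=outcome variable (difference score T2-T0b of the primary outcome measure"). It has a built-in safeguard: "the starting model will consist of all the significant primary mediators of Step 6 that have also been assessed in the control group". The next instruction is "The models will then be complemented with the secondary mediating factors described in Textbox 2", and the safeguard is not repeated there. Selection then follows one rule: "Mediating factors for which the indirect effect (a × b) is insignificant will be removed stepwise".

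The abstract describes the comparator as "an active control condition that solely consists of receiving psycho-educational emails". Under Randomization, a therapist is assigned only to participants in an experimental condition. No control-arm sessions are described anywhere.

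The Mediating Factors section defines secondary factors as those not measured during the intervention and points to Table 2 for the full list. Table 2 names five, and session count is not among them.

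**The concern.** Session count is a measure of treatment received. In an X–Z–Y model, path a should be the effect of randomisation on Z, and path b the effect of Z on outcome at fixed arm. A variable that exists in one arm only cannot play that part:

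- If Z is set to 0 for all controls, path a is the mean attendance in the treated arm and is significant by construction. Controls have no variation in Z, so path b comes entirely from comparing treated participants who attended more with those who attended less. That comparison is not randomised. The product a × b extends the slope down to zero sessions, and c' takes up the opposite amount.
- If Z is undefined in controls, path a cannot be estimated.

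The Mediators part of the Introduction names shortening the intervention as one use of knowledge about working mechanisms. A spurious finding about the number of sessions would bear directly on that kind of decision.

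**Working it through.** **Does session count enter Step 7?** Textbox 2 has one list that fits the reference in Step 7, namely the explored factors. Five of its six items correspond to the five secondary factors of Table 2; the sixth is session count. Step 6 works on growth trajectories of the primary mediators, so Step 7 is the only described step that could examine session count. Entry is therefore the natural reading, but the definition under Mediating Factors and Table 2 point the other way.

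**The plan's own numbers (Power Analyses).** With 330/3 = 110 per arm:
- 110 × 0.70 = 77 per experimental arm at T2.
- 110 × 0.85 = 93.5, given as 94 controls.
- 77 + 94 × 0.70 / 2 = 109.9, given as 110 completing each intervention.
- 220 × 0.90 = 198.

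All reproduce. The 77 is already net of 30% attrition, so it is not a suitable base for a further 30% of early stoppers. Under Nonadherence and Withdrawal, those who stop the intervention are still asked for T1, T2 and T3. The illustration therefore starts from 110 per arm with stoppers followed.

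**Assumptions, not in the document.** Up to 9 sessions (the intervention lasts 9 weeks); 30% stop after 1 to 8 sessions, uniformly, and the rest complete 9; outcome SD of 10 CIS points (this does not affect rejection rates); no treatment effect and no effect of sessions; stopping follows a threshold model whose latent variable correlates r with a poorer T2–T0b change. No document supplies r.

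**Formula check.**
- Mean sessions: a = 0.3 × 4.5 + 0.7 × 9 = 7.65.
- Variance: 0.3 × 25.5 + 0.7 × 81 − 7.65² = 64.35 − 58.52 = 5.83, so SD = 2.41.
- Covariance of sessions with outcome: −(9 − 4.5) × 0.348 × r = −1.565r outcome SDs, where 0.348 is the normal density at the 30% cut-off.
- Path b = −1.565r / 5.83 = −0.268r SD per session.
- a × b = 7.65 × (−0.268r) = −2.05r SD, which is −4.1 points at r = 0.2 and −6.2 at r = 0.3.

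**Simulation.** 4,000 runs per cell; least squares of Y on X and Z; SE(ab) = √(a²Var(b) + b²Var(a)); two-sided 0.05; 110 vs 110; all stoppers followed.

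| r | mean a × b | mean c' | a × b significant | total effect significant |
|---|---|---|---|---|
| 0 | −0.03 | +0.04 | 4.8% | 4.9% |
| 0.2 | −4.0 | +4.0 | 27% | 5.1% |
| 0.3 | −6.2 | +6.2 | 53% | 4.9% |
| 0.5 | −10.4 | +10.3 | 95% | 4.9% |

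The correlation of X with Z is about 0.91. With 110 treated and 94 controls, the rates at r = 0.2 and 0.3 are about 27% and 54% if every stopper gives T2 data, and about 14% and 27% if one third do. If one tenth do, they are roughly 8–9% and 11–13%.

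The simulation has one mediator, no stepwise selection and no second-semester data, although Step 7 uses both semesters.

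**The case against.** The strongest reply is textual. Secondary is a defined term in this article, and under that definition Step 7 adds only the five factors in Table 2, all questionnaire items at T0b and T1. Session count would then never enter, and the fault would be only that the article does not say how it will be explored. This stands as far as it goes: a reader might infer that the plan certainly enters session count, and the text does not establish that. But it leaves a listed mediator with no other described analysis, and the conflict between the places remains.

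The second reply is that only path a is guaranteed to be significant. This also stands. With stopping unrelated to outcome, the error rate is nominal, and if improvers stopped early the sign would reverse. A reader might infer that ordinary dropout will generally appear as mediation; that requires a correlation the document does not give. Nor do the numbers left after attrition, 77 and 94, support a larger headline rate, since they already exclude the 30% who leave. If those lost are the stoppers, hardly any variation in session count remains.

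Third, Step 7 also reports path coefficients and the total effect with 95% confidence intervals, so an attentive reader could see a near-zero total and an opposing c'. True, but the retention rule looks only at a × b, so the factor would stay in the final model.

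A reader might also infer that genuine mediators would be displaced from the final model. That was not computed, and nothing in the document shows it.

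**Conclusion.** The point holds in limited form. Textbox 2, Step 7 and the definition of secondary factors (Mediating Factors, Table 2) disagree on whether session count is a Step 7 mediator. On the natural reading it is, and its a × b would then not be an indirect effect of randomisation, whatever the correlation between stopping and outcome.

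The size of the false-positive risk rests wholly on assumption: about 27% at latent r = 0.2 and 53% at r = 0.3 with 110 per arm and complete follow-up of stoppers, lower with sparse follow-up, and about 5% at r = 0. These figures illustrate the mechanism and do not predict this trial. The analysis is exploratory. The document does not support reading this as a threat to the effectiveness result, because Step 1 does not use session count.

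**What to change.** Extend to every factor entered in Step 7 the condition the plan already sets for its starting model, "the significant primary mediators of Step 6 that have also been assessed in the control group", keeping only the part about assessment in controls. This takes number of sessions completed out of the X–Z–Y model, so the spurious indirect effect cannot arise. Align Textbox 2, the Mediating Factors section and Table 2 so that each states the status of session count in the same way.

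Report sessions completed descriptively by arm, or in a separate adherence analysis clearly labelled exploratory.

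The cost is some wording and the loss of one exploratory mediator. No new data are needed and the primary effectiveness test does not change. The Discussion says the paper was submitted before any data were analysed, so the clarification fits the purpose of publishing the plan.
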